#### Data monitoring

A study monitor who will not be involved in patient care, intervention, data collection and assessment, or study coordination will oversee all study procedures in accordance with Good Clinical Practice guidelines. The study monitor will also ensure that written informed consents have been obtained, that (e)CRFs have been created correctly (e.g., including ranges to avoid exceeding minimum and maximum values, including additional fields to add information to ensure proper recording of data), and that the data are stored securely in locked file cabinets and/or in the REDCap database. The study monitor will also assess the completeness and correctness of the data twice a year and provide technical support to other study staff.

#### Harms and adverse event reporting

Previous studies have shown that VR-based cognitive and relaxation interventions can be used safely in the ICU, even in patients with invasive MV [13, 19, 20]. Adverse events (e.g., unsafe physiological parameters, unintentional removal of catheters, endotracheal tubes, tracheostomy cannulas), whether or not related to the use of the RGS-ICU platform, will be collected and analyzed for all participants. No reason for interruption or suspension of the trial is foreseen. However, following the European Commission guidelines on the collection, verification and reporting of adverse events arising from clinical trials [63], in the event of a (serious) adverse event that poses a risk to participants or is causally related to the use of the RGS-ICU platform, the principal investigator may interrupt and/or suspend the trial, and the ethics committee and other relevant parties will be informed.

#### Auditing and protocol amendment

The study staff of each participating center will be responsible for complying with the study protocol and for reporting any deviation or request for modifications to the study coordinator and monitor and the principal investigator. All decisions regarding study procedures and protocol modifications will be made with consensus of the four partners, communicated to relevant parties and ethics committee for approval prior to implementation, and posted on Clinicaltrials.gov. However, in emergency circumstances, deviations from the study protocol may be made to protect the rights, safety and welfare of human subjects without prior ethics committee approval. Any deviation from the study protocol will be fully documented in the (e)CRF. For quality assurance, the study coordinator and monitor, principal investigator and ethics committee may have access to the source data and all study-related records, with the obligation to maintain strict confidentiality.

## Ethics and dissemination

### Consent or assent

The clinical staff in charge of patient screening and recruitment at each hospital will be responsible for obtaining written informed consent from the potential candidates and/or authorized representatives. The consent form contains all the information about the intervention and the data collected and evaluated and informs patients that they can exercise their right of access, modification, opposition and cancellation at any time. Patients are also informed that they may withdraw from the study at any time but that the data collected so far may continue to be used within the framework of the objectives of this trial unless they expressly object. Likewise, patients will be informed that they may be withdrawn from the study if deemed appropriate by the principal investigator, either for safety reasons, due to an adverse event derived from the intervention under study or due to non-compliance with the established procedures. The patient will receive an adequate explanation of the reason for the withdrawal of the study and will always continue to receive the standard medical treatment for his/her pathology. Finally, patients will be informed that their data may be shared with third parties (e.g., other research centers and universities), other countries, and the relevant regulatory authorities, while respecting the anonymity and confidentiality of the data, and within the framework of the objectives of this study. This trial does not involve collecting biological specimens.

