Patients will be constantly monitored during the intervention as part of standard ICU care. This will provide information on changes in mental status, mobility level and physiological parameters (e.g., peripheral oxygen saturation [SpO2], respiratory rate [RR] and heart rate [HR]), allowing the study staff to adapt the interaction, workload and duration of each session to the type of patient profile in real time. Adverse events (e.g., unsafe physiological parameters, unintentional removal of catheters, endotracheal tubes or tracheostomy cannulas) and tolerability issues (e.g., fatigue, extreme sleepiness, confusion) during the intervention will result in interruption or early termination of the session. Interruption or early termination of a session will not preclude participation in subsequent sessions if safety criteria are met (see “Safety and tolerability data” and “Harms and adverse event reporting” for details).

The intervention will be discontinued if patients voluntarily withdraw consent or, if they have not yet been able to give consent themselves, their authorized representative voluntarily withdraws consent, requests to stop receiving the intervention, are transferred to another ICU or die during ICU stay. At the discretion of the clinical staff, the intervention will also be discontinued if there are changes in the patient's medical condition, such as worsening disease, that make continued participation inadvisable or if there are safety concerns that poses a risk to participants. In the event of discontinuation of the intervention, patients will continue to receive standard ICU care. Participants should not participate in other RCT intended to stimulate cognition and provide relaxation during or after the ICU stay.

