#### Control condition: TAU group

Patients assigned to this arm will receive standard ICU care and should not participate in other RCT aimed at stimulating cognition and providing relaxation during or after the ICU stay.

Standard ICU care for RGS-ICU and TAU groups is based on the ABCDEF bundle, a set of recommendations to optimize recovery and outcomes in patients with critical illness [28, 29].

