### Sample size and power calculation

Sample size is based on the test of equality of two independent means for the primary outcome (objective cognition 12 months after ICU discharge) calculated using G-Power v3.1.9.7 software [48, 49]. Based on data from a randomized clinical pilot using the ENRIC platform [13], an eta squared effect size of 0.14 is anticipated. With a statistical power of 0.8 and a two-sided alpha level of 0.05, a minimum sample of 26 participants per group is needed to detect a Cohen's d effect size of 0.8 (total *n* = 52). Considering a dropout rate of 50% (15% during the ICU stay and 35% after ICU discharge), the minimum recruited sample needed for this RCT is 78 participants (*n* = 39 per group). Thus, at least 80 patients with critical illness (*n* = 40 per group) will be recruited, half of them in each participating hospital. However, since this RCT takes place in the ICU, it is to be expected that some dropouts will occur for reasons unrelated to the study itself (e.g., changes in health status that make continued participation inadvisable, mortality in the ICU, transfer to another ICU or withdrawal of consent previously given by an authorized representative). Thus, to maintain a sample size with sufficient power, these participants, estimated at 15%, will be replaced by new enrolments in a 1:1 ratio.

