### Allocation and blinding

After initial consent, patients will be assigned to one of the two study arms using the Research Electronic Data Capture (REDCap) randomization module. A blinded study coordinator, who will not be involved in patient care, intervention, data collection or assessments, will manage this computer-generated procedure. Due to the characteristics of the intervention, neither other study staff nor patients will be blinded. Data collection and assessments will also not be blinded. However, an independent statistician will perform data analysis in a blinded fashion.

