#### Statistical methods

Results will be presented as mean (standard deviation) or frequency (%). Depending on whether the data have a normal distribution, parametric or nonparametric statistics will be used. In case of non-normal data, the median (range) will be reported. To compare results between the RGS-ICU and TAU groups over time, intersubject and intrasubject analyses will be performed, adjusting for multiple comparisons when necessary (e.g., Bonferroni correction). More specifically, intention-to-treat and per protocol analyses will be used. To address missing data, a last observation carried forward analysis together with a complete-case analysis will be performed. Where appropriate, analyses will be controlled for age, sex, delirium, invasive MV, type and dose of pharmacological treatment and/or cognitive reserve (CRQ). Effect sizes will be reported for all significant and non-significant data. Statistical significance will be set at *p* < 0.05. Analyses will be performed using the most recent version of the Statistical Package for the Social Sciences (IBM SPSS Statistics for Windows, Armonk, NY: IBM Corp).

To compare sociodemographic and clinical data between the RGS-ICU and TAU groups, an intersubject analysis will be performed. Intervention characteristics (e.g., session duration, protocols performed, etc.), intervention safety (i.e., number of sessions terminated early due to unsafe events on physiological parameters) and intervention tolerability (e.g., fatigue, extreme sleepiness, confusion) in patients assigned to the RGS-ICU group will be analyzed using descriptive statistics. To compare experienced comfort (PEECE) between the RGS-ICU and TAU groups, an intersubject analysis will be performed. To compare cognition (MoCA, WAIS-IV Forward Digit Span, WAIS-IV Backward Digit Span, RAVLT, TMT, SCWT, FAS, WAIS-IV Digit Symbol-Coding, SDMT and PDQ-5), mental health (GAD-7, PHQ-9 and TOP-8), functionality (WHODAS 2.0) and HRQoL (SF-12) between the RGS-ICU and TAU groups over time, intersubject and intrasubject analyses will be used.

Other analyses will include comparison of changes in the intensity of dyspnea, pain, worry and sadness (VAS) before and after each session in patients assigned to the RGS-ICU group. To this aim, an intrasubject analysis will be used.

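### The investigator may withdraw patients from the study, not only from the sessions; those withdrawn in the ICU have no primary-outcome data, and one trigger exists only in the RGS-ICU arm

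*Protocol article*

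**What the plan says.** Several sections of the protocol article bear on what happens when a patient stops early.

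- **Consent or assent.** Patients are told that "they may be withdrawn from the study if deemed appropriate by the principal investigator", on the grounds "either for safety reasons, due to an adverse event derived from the intervention under study or due to non-compliance with the established procedures". What ends is study participation.
- **Experimental condition: RGS-ICU group.** A separate rule covers stopping the intervention. Its grounds include a worsening condition or safety concerns, as judged by clinical staff. The stated consequence is: "In the event of discontinuation of the intervention, patients will continue to receive standard ICU care". Outcome visits are not mentioned. For a single session: "Interruption or early termination of a session will not preclude participation in subsequent sessions if safety criteria are met".
- **Sample size and power calculation.** Changes in health status that make it inadvisable to go on are listed as dropout, beside ICU death, transfer and withdrawn consent, and "these participants, estimated at 15%, will be replaced by new enrolments in a 1:1 ratio".
- **Control condition: TAU group.** Controls also have obligations: they "should not participate in other RCT aimed at stimulating cognition and providing relaxation during or after the ICU stay".
- **Allocation and blinding.** Apart from the coordinator who runs the randomisation and the statistician, "neither other study staff nor patients will be blinded".
- **Statistical methods.** "More specifically, intention-to-treat and per protocol analyses will be used", with last observation carried forward (LOCF) and complete-case analysis for missing data.

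**The concern.** A patient whose sessions are stopped on safety grounds could be handled in three ways: sessions end and standard care goes on; the patient leaves the study; or the patient counts as a dropout and is replaced. Only the first is compatible with observing that patient at 12 months, and even there the text does not say so.

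The choice rests with an investigator who knows the allocation. One trigger, an adverse event derived from the intervention, cannot occur in a control. Non-compliance can occur in either arm, but daily sessions give the RGS-ICU arm more procedures to fail.

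If frailer or less tolerant RGS-ICU patients were withdrawn in this way, the 12-month comparison would set a partly selected arm against a less selected one. The planned intention-to-treat analysis is meant to prevent this, but it cannot use outcomes that were never collected.

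**Working it through.** **1. The plan's own figure.** An eta squared of 0.14 gives d = 2 × √(0.14/0.86) = 0.807, so the planned 0.8 agrees. A two-sample t-test with d = 0.8, two-sided alpha 0.05 and power 0.80 needs 25.5, rounded up to 26 per group (power 0.807 at 26). The stated 26 reproduces.

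**2. Can the planned analyses use a patient withdrawn in the ICU?**

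- The composite is built from the Digit Span, RAVLT, TMT, SCWT, FAS, Digit Symbol-Coding and SDMT measures (Outcomes). Table 3 schedules them only at 3 and 12 months.
- At ICU discharge only MoCA and PEECE are given (Table 2). Neither is part of the composite.
- LOCF therefore has no value to carry forward, and complete-case analysis omits the patient by definition.
- Replacement restores the number of patients but not the distribution, because new enrolments pass through the same filter.
- A patient withdrawn after the 3-month visit would have a 3-month value to carry forward, so the complete loss concerns withdrawals before that visit.

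**3. Which arm can each trigger reach?**

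| Trigger | RGS-ICU | TAU |
|---|---|---|
| Adverse event derived from the intervention | yes | no |
| Non-compliance with procedures | yes: sessions, visits, bar on other trials | yes: visits, bar on other trials |
| Safety reasons | yes | yes |

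**4. Size, under stated assumptions.** The documents give no withdrawal rate and no link between withdrawal and outcome. Assume that a fraction f is lost in the RGS-ICU arm only, namely those lowest on a latent score that has correlation ρ with the 12-month z-score, and that the true effect is zero. With q the f-quantile of the standard normal and φ its density,

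bias = ρ × φ(q) / (1 − f).

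| f (patients of 40) | φ(q)/(1 − f) | ρ = 0.3 | ρ = 0.5 |
|---|---|---|---|
| 5% (2) | 0.109 | 0.033 | 0.054 |
| 10% (4) | 0.195 | 0.058 | 0.097 |
| 15% (6) | 0.274 | 0.082 | 0.137 |

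Against the planned 0.8 SD this runs from 0.033/0.8 = 4% to 0.137/0.8 = 17%. With ρ = 0 the bias is zero.

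In a simulation (20,000 runs, t-test, 26 analysed per arm), the two-sided type I error at f = 15% was about 0.057 for ρ = 0.3 and 0.081 for ρ = 0.5, against 0.051 for ρ = 0.

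A cruder check gives the same order. If those lost would have scored δ lower than the rest, the bias is f × δ. With δ assumed to be 0.5–1.0 SD, this runs from 0.05 × 0.5 = 0.025 to 0.15 × 1.0 = 0.15 SD.

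**5. Why f stops at 15%.** The plan expects 15% ICU-stage dropout from all causes: 0.15 × 80 = 12 patients, or 6 of 40 per arm if shared equally. At f = 15% this one clause would account for the whole of that arm's allowance, so the last row is an upper end.

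**The case against.** The best defence is that the consent section reports what patients are told. It is permissive, sets no compliance threshold and names no response criterion. Stopping the intervention and leaving the study are different events, so rules for both can coexist. The 3- and 12-month visits are scheduled without an exception for patients whose sessions stop, and intention-to-treat is planned. A condensed article may also leave such detail to the full protocol.

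Part of this stands. The clause is discretionary and may be used rarely. But the article does more than stay silent. It names study withdrawal as a possible consequence of events that another section handles by stopping sessions, and it counts nearly the same change in health status as a replaceable dropout. No analysis plan can recover 12-month data that were not collected.

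Three stronger readings are tempting and are not supported:

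- **That the triggers act almost only in the RGS-ICU arm.** This is certain only for the adverse-event trigger. The other two can apply to controls, as the table above shows.
- **That the rule would remove the arm's poor responders.** Fatigue, sleepiness or confusion interrupts or ends a session and does not bar later ones. The safety section says the same of sessions ended early. Cooperative patients with delirium are admitted to sessions. Selective loss of frailer patients is possible, but it is an inference.
- **That harm follow-up is cut off.** The section on harms promises that adverse events will be collected and analysed for all participants. It does not say whether this continues after withdrawal by the investigator, which is worth stating.

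**Conclusion.** The point holds in a limited form. As written, an unblinded investigator may end study participation on grounds of which one can arise only in the RGS-ICU arm. A patient so withdrawn in the ICU contributes nothing to the primary comparison under either planned approach to missing data. That is at odds with the stated intention-to-treat analysis, and replacement does not repair it.

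The size is unknown. Under the assumed RGS-ICU-only loss of 5–15% and correlation of 0.3–0.5, the bias is about 0.03–0.14 SD. This is well below the planned 0.8, but enough at the upper end to raise the type I error noticeably. The bias favours RGS-ICU only if withdrawn patients would have had worse 12-month cognition. If withdrawal is unrelated to outcome, or if these patients are still assessed, this bias disappears. Losses of the same kind among controls would offset part of it.

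**What to change.** Reconcile the sections on the experimental condition, sample size, statistical methods and consent so that they say the following.

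1. Stopping the sessions for an adverse event, a safety concern or non-compliance is not withdrawal from the study.
2. Surviving patients who have not withdrawn consent to follow-up stay in adverse-event follow-up and attend the scheduled 3- and 12-month assessments. PEECE and MoCA are given at ICU discharge if the patient is mentally competent, as already planned.
3. These patients are analysed in the arm to which they were randomised, and stopping sessions does not by itself trigger replacement.
4. *Sessions stopped* and *consent to follow-up withdrawn* are recorded as separate events, each with reason and date, and reported by arm.

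Decisions on when to stop sessions stay with the clinical staff; the change concerns only what is observed afterwards. The cost is an amendment to the protocol and consent form, with ethics approval. No visits are added to those already scheduled.

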### Dissemination policy and access to data

The progress of the project will be regularly disseminated in the media and networks. Interim analyses will only be conducted to inform funders of the progress of the study, but no results will be published before the end of the trial, scheduled for summer 2026. Once the study is completed, results will be submitted for publication in peer-reviewed journals, presented at regional, national, and international scientific meetings, and disseminated to the public and other interested parties. At present, no publication restrictions are foreseen. The datasets and statistical code will be available upon reasonable request to the corresponding author(s) once the results have been published, as are the full protocol and informed consent materials.

## Discussion

This is a two-arm, parallel-group, superiority RCT aimed at evaluating the efficacy and safety of receiving early cognitive stimulation and relaxation as an adjunct to standard ICU care compared to receiving standard ICU care alone. This trial responds to the need to humanize intensive care [64], a new paradigm of human-centered ICU care that aims to actively involve patients in their recovery process, as intended by the RGS-ICU intervention.

This RCT builds on previous PoC and clinical pilots that demonstrated that neuropsychological e-health interventions based on VR techniques, whether immersive or not, used as an adjunct to standard ICU care, in addition to being safe for patients with critical illness [19], can help reduce anxiety during the ICU stay [20], as well as improve working memory performance after ICU discharge [13]. However, these studies were limited by methodological issues such as single-center designs, small sample sizes (n ≤ 21 subjects per group), heterogeneous diagnoses, interventions that included cognitive but not relaxation protocols, and absence of assessment of variables such as experienced comfort, subjective cognition, functionality and HRQoL.

In an attempt to overcome these limitations, the RGS-ICU trial has been designed, whose main strengths include a multicenter design, strict inclusion/exclusion criteria, an adequately powered sample size to test the primary outcome (i.e., objective cognition 12 months after ICU discharge), the use of an enhanced and optimized e-health intervention combining cognitive protocols to stimulate the brain with relaxation videos to promote stress and anxiety reduction, and the administration of a full neuropsychological battery to characterize the cognitive, mental health, functional and HRQoL profile of survivors of critical illness. This trial will also benefit from monitoring patients' physiological parameters as part of standard ICU care to ensure the safety of the intervention and that it is adapted to their mental status and mobility level in real time. In contrast, its open design is a limitation that will be compensated by blinding the data analysis by an independent statistician. Following SPIRIT guidelines for reporting study protocols [22], the sample size has been calculated for the primary outcome, so the study may be underpowered for test other outcomes. The use of self-reported measures to assess mental health may also be a limitation of the study.

By relaxing patients and increasing brain activity in areas related to cognition and emotion, as demonstrated in previous PoC and clinical pilots using a surrogate measure of cognitive function such as HRV [13, 19, 20], the RGS-ICU intervention could help preserve neuropsychological functioning in survivors of critical illness, especially in patients who are mentally vulnerable, such as elderly patients, patients with delirium or patients undergoing invasive MV. Thus, the results of the present trial could contribute to establishing a new paradigm of supportive care adjuvant to standard ICU care (and perhaps even superior to standard ICU care alone) to improve neuropsychological outcomes during and after the ICU stay. In addition to the clinical impact, the results could also have a relevant socioeconomic impact by accelerating the recovery process. In fact, interventions similar to RGS-ICU but focused on physical and functional rehabilitation to prevent ICU-acquired muscle weakness have shown a reduction of ICU admission of up to 1.4 days [65].

Given that the RGS-ICU platform interprets the physical movements of patients' upper extremities to interact with cognitive multimedia content, it is anticipated that the results of the present trial may also encourage the introduction of rehabilitation protocols that combine physical and cognitive exercises with relaxing videos in a single technological tool that addresses all three dimensions of PICS at once. Future trials should also consider extending early cognitive stimulation and relaxation beyond ICU stay to contribute to the rehabilitation and recovery process of survivors of critical illness affected by PICS.

